### Adverse events and safety

This study strictly adheres to relevant standards to ensure the compliance of equipment and personnel with these standards. Therapists will provide professional supervision throughout the training to minimize accident risks. Despite extensive preventive measures, potential risks such as falls, ankle sprains, soft tissue edema, and seizures remain. To address these, an emergency response plan has been developed, and risks such as equipment damage have been considered.

All adverse events and unexpected reactions during the study will be promptly recorded and assessed. In the event of an adverse event, participants’ changes in condition will be immediately reported, and necessary treatment will be provided until stability is achieved. The research team will evaluate the relationship between adverse events and the treatment.

### Participant compliance

The following methods are implemented in this study to guarantee the validity of the experimental data and enhance participant compliance:

All trial protocols, procedures, and requirements are clearly explained to participants and researchers, along with detailed operational guidelines.Comprehensive training is provided for participants and researchers to ensure a clear understanding of the study’s objectives, roles, and responsibilities.Regular supervision, feedback, and guidance are established to assist therapists in tackling challenges during training.Assessment schedule reminders are sent via email and phone to participants, with flexible arrangements to maintain data collection continuity and integrity.

### Data collection and management

Primary outcome indicators will be collected using standardized instruments to ensure data accuracy and objectivity. Secondary outcome indicators will be assessed independently by two professional therapists, with results cross-verified. Any discrepancies will be discussed to reach a consensus.

For patients who withdraw or change their training regimen, the time and reasons for withdrawal will be documented to determine whether their data will be included in the final analysis. If corrections are needed for original records, a dated statement explaining the changes must be attached. All original study documents and copies will be stored for inspection.

Data entry will use an electronic data capture system with double data entry to minimize errors. Each participant’s electronic case report form will be backed up. Project administrator accounts will be created to ensure that researchers have appropriate data access permissions based on their roles, responsibilities, and confidentiality agreements. Data uploaded from each center will be monitored by a third-party quality control organization (The Fourth People’s Hospital of Kunshan).

### Statistical analysis

Statistical analysis will be performed using SPSS software (V.26.0). Data normality will be assessed using the Shapiro–Wilk test, and variance homogeneity will be evaluated using Levene’s test. Normally distributed continuous variables will be expressed as mean ± standard deviation, and non-normally distributed continuous variables will be presented as median (interquartile range). Descriptive statistics will be used to summarize baseline demographic and clinical characteristics.

All statistical analyses will be conducted using linear mixed-effects models (LMMs) to account for repeated measurements, individualized intervention exposure, and inter-individual variability. Participant identity will be included as a random intercept, and time (baseline, post-intervention, follow-up) will be specified as a fixed effect. The primary outcome will be modeled within this framework. For secondary outcomes and exploratory analyses involving multiple comparisons, the Holm–Bonferroni correction will be applied to control the family-wise error rate. The primary outcome will not be adjusted for multiplicity.

Stroke phase (recovery vs. chronic) and center will be included as fixed effects. Time-by-phase interactions will be examined to explore potential differences in longitudinal recovery trajectories between stroke phases. To address heterogeneity in intervention exposure inherent to the sequential adaptive design, cumulative training dose and step-specific duration will be incorporated as time-varying covariates. This approach allows adjustment for individual differences in progression speed and treatment intensity. In the presence of non-normal outcome distributions or convergence difficulties, generalized estimating equations (GEEs) with appropriate link functions will be conducted as sensitivity analyses to assess the robustness of the primary findings.

Missing data will be handled under the missing-at-random assumption using the maximum likelihood estimation inherent in LMMs, which allows inclusion of participants with incomplete follow-up data without listwise deletion. Sensitivity analyses will be conducted to assess robustness. Effect sizes will be reported as model-estimated mean differences with 95% confidence intervals. Standardized effect sizes (Cohen’s d) will also be calculated where appropriate to facilitate clinical interpretation.

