### Sample size estimation

The sample size calculation was based on an internal pilot dataset (n = 30) collected at the coordinating center prior to trial registration, using the minimal knee flexion angle during the swing phase on the hemiparetic side as the primary outcome measure. The pilot study was approved by the Medical Ethics Committee of the Affiliated Changshu Hospital of Soochow University (Approval No. X202265), and pilot participants were not included in the current trial (19). The use of pilot data to inform feasibility and parameter estimates for subsequent studies is supported by methodological guidance on pilot studies and pilot-informed trial planning (19, 20).

In the pilot dataset, the mean pre–post change in the primary outcome was 1.2 degrees, with a standard deviation of the within-subject change score of 6.36. The standardized effect size was therefore d = 0.1887 (d = Δμ/SDΔ). Although the pilot-derived effect size was small, the minimal knee flexion angle represents a joint-level biomechanical marker of neuromuscular coordination (21). Variations in swing-phase knee flexion primarily reflect changes in limb advancement mechanics and inter-joint coordination rather than global functional performance. Therefore, even relatively small angular differences may provide meaningful biomechanical information relevant to post-stroke gait recovery. Sample size estimation was performed using G*Power (difference between two dependent means, matched pairs). With an effect size (dz) of 0.1887, a one-sided significance level (*α*) of 0.05, and statistical power (1−β) of 0.80, the required minimum sample size was calculated to be 174 patients. A one-sided test was adopted, given the directional hypothesis that GCST would improve, rather than worsen gait performance. To account for potential attrition and to ensure balanced recruitment across centers, the planned recruitment target was set at 180 participants across four participating centers (approximately 45 participants per center). Based on pilot observations and adherence-enhancing procedures implemented in the study protocol, the anticipated attrition rate is expected to remain low. Healthy controls were not included in the sample size calculation and were recruited solely to provide normative reference values.

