Time points: t_0_: Baseline (patients); t_0*_: baseline (healthy controls); t_1−_ t_4_:post-step assessments (after the completion of steps B–E, respectively); t_5_: semi-annual follow-up; t_6_: annual follow-up. MA, muscle architecture; sEMG, surface electromyography; COP, center of pressure; PPD, plantar pressure distribution; PS, postural sway; 3DGA, three-dimensional gait analysis; BRS, Brannstrom recovery stage; FMA-LE, Fugl–Meyer Lower Extremity; FAC, functional ambulation category; SLS, single-leg stance; BBS, Berg Balance Scale; MMT, manual muscle testing; MAS, Modified Ashworth Scale; SF-36, 36-Item Short Form Health Survey; BI, Barthel Index; TEAE, treatment-emergent adverse event; Center indicators: √, Suzhou and Kunshan sites; ○, Changshu site; □, Zhangjiagang site.

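### The primary analysis model does not match the powered paired test or the gait-analysis visits, so the one-sided 5% level and 80% power are not secured

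*Protocol article*

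**What the plan says.** Protocol article, Sample size estimation: the calculation is for a "difference between two dependent means, matched pairs", with a mean change of 1.2 degrees, an SD of change of 6.36, dz = 0.1887, a "one-sided significance level (*α*) of 0.05" and power 0.80. It gives 174, and 180 are to be recruited. The choice of side is explained: "A one-sided test was adopted, given the directional hypothesis".

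Protocol article, Statistical analysis: "Participant identity will be included as a random intercept", and "time (baseline, post-intervention, follow-up) will be specified as a fixed effect". The primary outcome is to be modelled in this framework. Phase and center are further fixed effects, and cumulative dose and step-specific duration enter as time-varying covariates. Holm correction is reserved for secondary and exploratory analyses: "The primary outcome will not be adjusted for multiplicity". On reporting: "Effect sizes will be reported as model-estimated mean differences with 95% confidence intervals". The section does not say whether the model test is one- or two-sided.

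Protocol article, Assessment and follow-up, Table 1: gait analysis is marked at t0 to t4, and t5 and t6 are blank. The legend defines t1 to t4 as "post-step assessments (after the completion of steps B–E, respectively", and t5 and t6 as the semi-annual and annual follow-ups.

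Protocol article, Objectives: the third objective is to observe what each step does to posture and gait.

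**The concern.** The article powers one clearly described test and then describes a different analysis. The three time labels do not fit the five visits at which the primary outcome exists. A reader cannot tell whether the primary result is the change to the end of step E, an average over all post-step visits, or any one of four visit contrasts. The interval level does not match the sidedness of the powered test either.

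There is no stroke comparator, so the within-person change in this one outcome carries the efficacy claim. The planned effect is small (dz = 0.1887), so the choice of contrast and level can decide whether the study is called positive. The third objective also cannot be answered from a factor that gives all four steps one label.

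**Working it through.** **Inputs.** From Sample size estimation: mean change 1.2 degrees, SD of change 6.36, dz = 0.1887, one-sided alpha 0.05, power 0.80, N = 174, target 180. From Table 1: gait analysis at t0, t1, t2, t3 and t4 only.

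**1. Reproducing the plan's figure.** n = ((z0.95 + z0.80)/dz)² = ((1.645 + 0.842)/0.1887)² = 173.6, so 174. The exact noncentral t gives 175. The figure is confirmed, and only as a one-sided 5% test of one contrast. At 180, exact power for that test is 0.81.

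**2. Time factor against visits.**

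| Level in the model | Visits with the primary outcome |
|---|---|
| baseline | t0 |
| post-intervention | t1, t2, t3, t4 if all post-step visits are included |
| follow-up | none (t5 and t6 have no gait analysis) |

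**3. Literal reading: t1 to t4 pooled.** Assume that benefit builds evenly to 1.2 degrees at t4.
- Effect: 1.2 × (0.25 + 0.50 + 0.75 + 1.00)/4 = 1.2 × 0.625 = 0.75 degrees.
- Averaging four visits also reduces variance. Under equal correlation, with within-person variance s² per visit, a single change has variance 2s² and the pooled change has s²(1 + 1/4) = 1.25s². The ratio is 0.625, so the SD is 6.36 × √0.625 = 5.03.
- Standardized effect: 0.75/5.03 = 0.149, which is 79% of 0.1887.
- Power at 180, one-sided 5%: noncentrality 0.149 × √180 = 2.00, power about 0.64 against 0.81.

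The direction depends on the build-up. If the whole 1.2 degrees appeared after the first step, pooling would raise power (1.2/5.03 = 0.239, above 0.1887).

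**4. Other reading: each post-step visit tested against baseline.** Four one-sided 5% contrasts without adjustment, by simulation under the null:

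| Correlation between contrasts | Family error |
|---|---|
| 0.5 | 0.144 |
| 0.7 | 0.120 |
| 0.8 | 0.105 |

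Readings 3 and 4 exclude each other, so their consequences do not add up.

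**5. Test level against interval.** A two-sided 95% interval corresponds to one-sided 2.5%. At 180 the standard error of the change is 6.36/√180 = 0.474 degrees. The one-sided 5% test is positive above 1.653 × 0.474 = 0.78 degrees, while the 95% interval excludes zero only above 1.973 × 0.474 = 0.94 degrees. A mean change between 0.78 and 0.94 would be a positive test beside an interval that includes zero. If the 95% interval decided the result, power at 180 would be 0.71, and 223 participants would be needed for 0.80.

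**6. Covariates.** Cumulative dose is zero at baseline and rises with time. A time contrast adjusted for it is no longer the raw pre-post change that was powered. The documents give no figures to size this.

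**The case against.** The strongest reply is that the plan means one contrast. The sample size speaks of a single pre-post change, and treatment ends on passing the step E test, so post-intervention could simply mean t4. With no gait analysis at follow-up, one contrast then remains, and leaving it unadjusted is proper. The step contrasts could sit among the exploratory analyses under Holm. The three labels may also be generic wording for all outcomes, and some of those (FAC, SF-36, Barthel Index) do have follow-up data. This is a reasonable guess at the intent, and it is why the family error is conditional. But the text does not say it: under that reading t1 to t3 have no level in the stated factor, and the primary outcome has no version of the model of its own.

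Three stronger claims may tempt a reader, and the documents support none of them.
- *That four unadjusted primary tests are planned.* The number of contrasts is never stated; 10 to 14% applies only on that reading.
- *That the 95% interval breaches the stated error rate.* It is a reporting rule and nowhere the decision rule. If it were, the one-sided error would be 2.5%, below the planned 5%; only power would fall.
- *That the random intercept makes the standard error of t4 minus t0 too small.* That needs a correlation that decays between visits and independent residuals. The article gives no correlations and no residual covariance, which is a detail commonly left to the full analysis plan.

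A mixed model using all five visits could also have more or less power than the paired test; the correlations needed to say which are not given.

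**Conclusion.** The point holds as a mismatch: the primary contrast, its sidedness and its level are not fixed consistently, so the stated level and power are not secured. It does not show that they fail. What rests on the text alone is the empty follow-up level for the primary outcome, four visits without levels of their own, the absence of a named primary contrast, and 95% intervals set against a one-sided 5% design.

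The sizes are conditional. Power of about 0.64 instead of 0.81 at 180 assumes pooling, even build-up and equal correlation. A family error of 10 to 14% assumes four separate tests with contrast correlation 0.8 to 0.5. Power of 0.71 at 180 assumes that the 95% interval decides. The plan's own 174 is correct for the test it describes. The change should be made, because the wording invites a weaker or ambiguous primary analysis and is cheap to correct.

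**What to change.** For gait-analysis outcomes:
1. Use a five-level time factor, t0 to t4, and keep the follow-up levels for outcomes measured at t5 and t6.
2. Name t4 minus t0 as the single primary contrast, estimated without cumulative dose and step duration, so that it is the pre-post change that was powered. Use those covariates in a secondary analysis.
3. Put the t1, t2 and t3 contrasts with baseline in the Holm family; this also serves the third objective.
4. Use one level throughout: either one-sided 5% with a 90% interval (or a one-sided 95% bound), or two-sided 5% with a 95% interval and power restated as about 0.71 at 180 (223 for 0.80).

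As an optional safeguard, allow a less restrictive within-person covariance over t0 to t4, for example unstructured (15 parameters).

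The cost is analysis wording, plus a less favourable stated power if the 95% interval is kept as the standard. No visit or measurement changes.

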## Methods and analysis

### Study design

This multicenter, prospective, interventional sequential study is led by the Affiliated Suzhou Hospital of Nanjing Medical University. Physicians will recruit hemiparetic stroke inpatients in the recovery phase and the chronic phase from four hospitals in Suzhou—The Affiliated Suzhou Hospital of Nanjing Medical University, The Affiliated Kunshan Hospital of Jiangsu University, The Affiliated Changshu Hospital of Soochow University, and The Gangcheng Rehabilitation Hospital of Zhangjiagang—and 30 healthy adults through the hospitals’ official media. Recruitment is scheduled to begin in October 2025 and will be completed by March 2026. Each participant will be followed for 12 months, so data collection, including follow-up, will conclude in March 2027. Data cleaning and statistical analysis will be conducted from April to June 2027, with primary results expected by July 2027. The study adheres to the SPIRIT guidelines to guarantee high-quality research (12), with the SPIRIT schedule presented in Figure 1 and the specific process illustrated in Figure 2.

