### Inclusion and exclusion criteria

The inclusion criteria for patient participants in the study are as follows:

Patients diagnosed with unilateral cerebral infarction or hemorrhage by CT or MRI;First occurrence of stroke with a clearly documented stroke onset date and currently in either the recovery phase (3–6 months post-stroke) or the chronic phase (≥6 months post-stroke) at the time of enrollment (15);Patients aged between 40 and 70 years;Those able to cooperate during examinations and follow simple instructions;Those exhibiting lower-extremity motor function impairment and hemiparetic gait;Those with the ability to stand independently for 2 min (provide stable center-of-pressure measurements in static balance assessments) (16) or to complete more than five consecutive gait cycles to ensure reliable kinematic data in three-dimensional gait analysis (17); andThe non-affected side has no significant coordination impairments and has muscle strength above grade 4 (ensuring the ability to participate in weight-bearing postural training while minimizing fall risk) (18).

The exclusion criteria for patient participants in the study are as follows:

Cerebellar injury or significantly reduced muscle tone.History of lower-extremity nerve, muscle, or skeletal system diseases or surgeries.Presence of lower-extremity joint pain or exhibiting significant foot inversion, clonus, or requiring botulinum toxin injection prior to training.Currently participating in other clinical trials.Severe diseases such as high-risk epilepsy or major cardiac conditions.Poor compliance or inability to complete the study interventions.

The healthy control group will be matched to the stroke patients for sex, age, and body type. They must be free of lower-extremity nerve, muscle, or skeletal diseases; pain; or surgery, which ensures their data reflects a healthy state.

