## Discussion

This multicenter, prospective, sequential study assesses the GCST’s efficacy in optimizing hemiparetic stroke patients’ gait and its underlying mechanisms. Conducted across general hospitals, the study enhances sample heterogeneity and representativeness and boosts the clinical applicability of its findings.

A key objective is to clarify the deficits and causes of posture adjustment in hemiparetic stroke patients. Postural regulation, the ability to dynamically adjust muscle tone to maintain balance during movement, is fundamental for motor and behavioral control. It is governed by a hierarchical neural control system spanning from the cerebral cortex to the spinal cord and is often impaired in patients with central neural damage. This impairment affects gait and extremity coordination, which rely on intact postural regulation. Conventional posture adjustment assessments typically focus on stability rather than directional control. This study innovatively uses the time patients maintain standard alignment under external force interference as a criterion to evaluate critical posture adjustment ability. This method is expected to more accurately reflect the posture adjustment ability of patients in a non-compensatory state. Sequential interventions allow the observation of GCST’s impact on coordination, posture, and gait recovery, helping to determine treatment benefits and prognosis in patients with varying stroke characteristics.

Another objective is to evaluate the GCST’s clinical effectiveness. Previous research indicates that the angle of force application in GCST significantly affects muscle recruitment (10). To achieve comprehensive muscle activation, patients must complete multidimensional GCST steps ranked by difficulty, with intervention progressing step by step from the sagittal plane, through the coronal plane, to the horizontal plane. This approach may activate the brain’s sensory-motor cortex, thereby promoting motor learning (40) and enhancing postural regulation.

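### Stroke phase is observed, not assigned, and the model names no baseline prognostic covariate, so the exploratory time-by-phase contrast may reflect case mix rather than disease duration

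*Protocol article*

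**What the plan says.** Under Study design, phase is defined from the interval between stroke onset and baseline assessment: 3–6 months is recovery, 6 months or more is chronic. Nobody is assigned to a phase. Both groups come from the same source: "Physicians will recruit hemiparetic stroke inpatients in the recovery phase and the chronic phase from four hospitals in Suzhou". Both must meet the same entry criteria, among them "Those exhibiting lower-extremity motor function impairment and hemiparetic gait".

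The Statistical analysis section lists the terms of the mixed model:

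- For repeated measures: "Participant identity will be included as a random intercept", with time as a fixed effect.
- For group terms: "Stroke phase (recovery vs. chronic) and center will be included as fixed effects".
- For the amount of training received: "cumulative training dose and step-specific duration will be incorporated as time-varying covariates".
- For the comparison of phases, the wording is exploratory: "Time-by-phase interactions will be examined to explore potential differences in longitudinal recovery trajectories between stroke phases".

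Baseline data have one stated use: "Descriptive statistics will be used to summarize baseline demographic and clinical characteristics".

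The link from phase to disease duration is made elsewhere. The Background names variation of step effects with disease duration as an open question. The first objective relates postural deficits to lesion location and disease duration in order to clarify causes. Study design says the phase windows reflect time-dependent recovery processes.

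**The concern.** A chronic-phase participant is someone whose gait deficit has lasted to 6 months or beyond, with no upper limit, and who is an inpatient at that point. A participant at 3–6 months has not passed through the same filter. The groups may therefore differ in severity, age or the proportion with haemorrhage for reasons other than elapsed time.

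Time-by-phase is the only disease-duration comparison specified for the longitudinal outcomes. It is a contrast in change. A constant difference in level between phases falls to the phase main effect and does no harm to it. A baseline factor that differs between phases and also predicts change does bias it, and the model contains no such factor. Entering one as a main effect only would not help, because it would adjust levels and not change.

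At stake is the reading of the phase comparison. A difference in trajectories could be reported as a consequence of disease duration when it came from who was recruited in each phase.

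**Working it through.** **The plan's own figure.** There is none for the phase contrast. The inputs come from Sample size estimation: mean change 1.2 degrees and SD of change 6.36, so d = 1.2/6.36 = 0.1887. The stated minimum of 174 reproduces: the normal approximation, one-sided 5% and 80% power, gives 173.6, and the exact noncentral t gives 175. The point here does not depend on that number.

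**Number per phase.** The documents give no phase split; an equal split is assumed. Table 1 schedules 3DGA, which supplies the primary outcome, at Suzhou, Kunshan and Changshu but not at Zhangjiagang. At about 45 per centre that is 3 × 45 = 135 patients, or about 67 per phase.

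**Formulas.** Let r be the correlation of baseline severity with change, and D the severity gap between phases in SD units. Both are assumptions. With no true phase effect:

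- Bias in the phase contrast of change = r × 6.36 × D.
- SE = 6.36 × √(2/67) = 1.099 degrees.
- False-positive rate = P(|Z + bias/SE| > 1.96).

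| D | r | Bias (degrees) | Bias/SE | False positives |
|---|---|---|---|---|
| 0.5 | 0.2 | 0.64 | 0.58 | 8.9% |
| 0.5 | 0.3 | 0.95 | 0.87 | 14.0% |
| 0.5 | 0.4 | 1.27 | 1.16 | 21.2% |
| 0.2 | 0.2 | 0.25 | 0.23 | 5.6% |
| 0.2 | 0.3 | 0.38 | 0.35 | 6.4% |
| 0.2 | 0.4 | 0.51 | 0.46 | 7.5% |

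For scale, the mean change used for planning is 1.2 degrees.

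**If all 180 supplied the outcome.** With 90 per phase, SE = 6.36 × √(2/90) = 0.948. The bias is the same, and the D = 0.5 row runs from 10.3% to 26.9%.

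**Does adjustment remove it?** Change scores were simulated with 90 per phase, r = 0.3, D = 0.5, no true phase effect and 3,000 runs. Without severity the mean bias was 0.91 degrees and rejection was 16.4%. With severity in the model they were −0.04 degrees and 4.7%. A covariate in a model for change corresponds to a covariate-by-time term in the mixed model.

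**Limits.** This is a two-sample calculation on change scores, not the planned mixed model with dose and step-duration terms. It shows scale only.

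**The case against.** Several counter-arguments have force.

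- **The model adjusts for more than centre.** This is true: it also includes cumulative dose and step-specific duration. These are post-baseline and follow from how fast a patient progresses. They do not replace baseline severity, and may absorb part of a real phase difference.
- **Imbalance is not shown.** Entry criteria are the same in both phases, all patients are inpatients, and recovery-phase patients also have a deficit lasting at least 3 months. A reader might infer that severity differences will appear as duration effects. The documents do not support that: they give no severity by phase, and only severity that predicts change matters. The most that can be said is that it may happen.
- **The contrast is exploratory.** The Statistical analysis section speaks only of exploring differences between phases, and the objective on GCST effects mentions neither phase nor duration. A reader might infer that time-by-phase is the trial's declared answer on duration. That is too strong: the tie comes from the Background, the first objective and the definition of the phases. The Discussion's remark about "helping to determine treatment benefits and prognosis in patients with varying stroke characteristics" does not mention duration and adds nothing here. The exploratory label lowers the weight of the result but leaves the confounding in place.
- **The threshold may be stricter.** Holm–Bonferroni applies to exploratory analyses with multiple comparisons, so 5% may not be the cut-off used. The bias in degrees is unaffected.
- **FMA-LE at enrolment follows the duration in question.** It may partly result from it, so adjusting could remove a real duration effect. This stands, and it rules out naming the FMA-LE-adjusted estimate as the disease-duration result. Age and stroke type are not open to this objection.
- **Covariates may be in an unseen analysis plan.** They may. But the article sets out the model terms, and the point concerns those terms.

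**Conclusion.** The concern holds in limited form. Phase is observed, no baseline prognostic covariate is named, and the exploratory time-by-phase contrast may therefore reflect case mix that predicts change. Direction and size are unknown.

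The range runs from close to nominal (about 6% to 8% false positives at a 0.2 SD gap) to material (about 9% to 21%, with 0.64 to 1.27 degrees of spurious difference, at a 0.5 SD gap). It rests on assumed correlations of 0.2 to 0.4, an equal phase split, about 67 per phase and the pilot SD.

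A reader might infer that the primary pre-post result or the sample size is also undermined. This point does not reach either: it concerns only how phase differences are estimated and described.

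**What to change.** 1. Keep the planned time-by-phase estimate. Beside it, report one adjusted for age and stroke type (infarct or haemorrhage), each with its interaction with time, and for centre-by-time.
2. Add a sensitivity model that also includes baseline FMA-LE and its interaction with time. Omit this when FMA-LE is the outcome. State that FMA-LE at enrolment may partly be a consequence of duration.
3. Describe all phase contrasts as associations, not as effects of disease duration.

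No new data are needed: age and stroke type are known at entry, and Table 1 schedules FMA-LE at baseline at all four sites.

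The cost is extra parameters and a somewhat wider interval for the phase term. For the primary outcome, with three centres and categorical time over t0 to t4 (four contrasts), age, stroke type and two centre indicators add 4 × 4 = 16 interaction parameters. FMA-LE adds 4 more, about 20 in all.
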